#### *Other advertising*

Posters will be placed in community centres, primary care practices and high street audiologists, to explain to the public what ISSNHL is, and that urgent treatment may be needed. The process will be coordinated by local ENT trainees working with INTEGRATE. The poster will also be made available in electronic format for information screens within waiting rooms. This approach aims to reach those participants who may not normally present to health care and do not use social media.

The trial team will work with hearing related charities to advertise and raise awareness of the trial to their members, with the aim to cover as much of the target population as possible.

Potential eligible participants will be identified by clinicians at participating sites following referral to the ENT unit from GPs, Emergency Departments, and audiology services (hospital, community or high street). The participant's clinicians will then alert a member of the trial team at the site.

### **6.3 Screening and enrolment**

An ENT clinician will confirm the diagnosis of ISSNHL via a pure tone audiogram. The potential participant will be asked by the clinical team if they are willing to speak to a member of the site research team to find out about the trial in more detail and to perform a complete eligibility assessment.

A medically qualified doctor who is delegated the task on the **STARFISH Site Signature and Delegation Log** will confirm eligibility. Investigators should consider the participant's medical history when determining if the sudden sensorineural loss is idiopathic. Pre-existing conditions such as ipsilateral Meniere's disease or multiple sclerosis that represent a high chance of being the aetiology for the hearing loss would make the participant ineligible for enrolment.

If the participants meet all the eligibility criteria and confirm that they are willing to take part in the trial, they will be asked to formally consent to participate in the trial as described in section 5.

Details of all participants approached about the trial will be recorded electronically on the **STARFISH Participant Screening/Enrolment Log**, which is part of the trial system. Since screening will occur prior to the participants providing consent, they will be identified by their sex, year of birth and date of screening only on the screening log.

### **6.4 Randomisation**

#### **6.4.1 Randomisation System**

Randomisation will be provided by BCTU using a secure online system (available at <https://www.starfish.bctu.bham.ac.uk>), thereby ensuring allocation concealment. Unique login usernames and passwords will be provided to those who wish to use the online system and who have been delegated the role of randomising participants into the trial as detailed on the **STARFISH Site Signature and Delegation Log**. These unique login details must not be shared with other staff and in no circumstances should staff at sites access the system using

---

another person's login details. The online randomisation system will be available 24 hours a day, 7 days a week, apart from short periods of scheduled maintenance.

In the event of the online system being unavailable, a telephone toll-free randomisation service ([name]) is available Monday to Friday, 09:00 to 17:00 UK time, except for bank holidays, government guided closures and University of Birmingham (UoB) closed days.

#### 6.4.2 Randomisation Procedure

After participant eligibility has been confirmed and written informed consent has been received, the participant can be randomised into the trial using the online system. All questions and data items on the online randomisation form must be answered prior to a potential participant being randomised into the trial and trial number being issued.

Following randomisation, a confirmatory email will be sent to the local PI and the delegate who carried out the randomisation.

The local research team should add the participant to the **STARFISH Participant Recruitment and Identification Log**, which links participants with their trial number. The PI must maintain this document securely, which is not for submission to BCTU and it should be held in strict confidence.

#### 6.4.3 Randomisation Method

Participants will be randomised at the level of the individual in a 1:1:1 ratio to either oral steroid only, intratympanic steroid only, or combined oral and intratympanic steroid treatment. A minimisation algorithm will be used within the online randomisation system to ensure balance in the treatment allocation over the following variables:

- Hearing loss severity pure tone average (PTA) at 0.5, 1, 2 and 4 kHz (mild/moderate less than 70dBHL; severe/profound 70dBHL or greater)
- Time since onset of hearing loss ( $\leq 14$  days;  $> 14$  days)
- New vertigo since onset of hearing loss (participant reported yes; no)
- Site

To avoid the possibility of the intervention allocation becoming predictable, a 'random element' will be included in the minimisation algorithm. Full details of the randomisation specification will be stored in a confidential document at BCTU.

### 6.5 Blinding

Participant blinding is not required given the method of primary outcome assessment, which is objective from the perspective of the participant. PPI during study development also suggested that knowledge of treatment allocation is unlikely to (directly) influence the primary outcome. It is also not practical given the different routes of drug administration between the arms of the trial.

The audiologist assessing the primary outcome (the pure tone audiogram) will be blinded to the randomised treatment allocation (18) as the outcome can be considered subjective from the perspective of the assessor. The ENT team member reviewing the participant routinely at that time will examine the ear prior to audiological testing and confirm to the audiologist that

---

the ear is appropriate for testing, without disclosing the treatment allocation. Findings that may make the ear non-appropriate may be earwax or an infection. Wax will be removed to allow testing to proceed, and an infection will be treated and testing arranged at the nearest opportunity. If there needs to be a delay in testing, this will be recorded with the reason. The audiologist therefore will not need to look in the participant's ear.

In addition, where feasible, the pre-injection PTA tests should be conducted by an audiologist not recording later outcomes for the trial. The audiologist(s) performing the pre-injection audiogram and outcome testing will be recorded allowing assessment for outcome bias. In the small proportion where the same audiologist performs both tasks and would therefore be unblinded to the pre-treatment hearing thresholds.

## 6.6 Informing the participant's GP

If the participant has agreed, the participant's GP will be notified that they have enrolled in the STARFISH trial, using the **STARFISH GP Letter**.

## 7 TRIAL INTERVENTION

### 7.1 Trial intervention and dosing schedule

Participants will be randomised to receive:

- Oral steroid (Prednisolone as tablets) 1mg/kg/day up to 60mg/day for 7 days.

OR

- Intratympanic steroid (Dexamethasone) three intratympanic injections 3.3mg/ml or 3.8mg/ml spaced 7±2 days apart (see below for technique).

OR

- Combined oral (Prednisolone) and intratympanic (Dexamethasone) steroid as described above, with the first intratympanic injection occurring within four days of starting oral steroids.

### 7.2 Steroid dose calculation

The dose of prednisolone will be based on the participant's body weight. Body weight should be measured in the clinic or estimated based on a weight recorded within 12 months used as a reference. In standard clinical practice, participants are not weighed prior to dosing, and a weight estimate used instead. This is appropriate given the safety profile of the intervention, and the lack of a requirement for strict dosing by weight. In many circumstances, participants will be seen out-of-hours when a requirement for weight measurement may delay urgent treatment. A dose of 1mg/kg/day should be calculated up to a maximum dose of 60mg/day. Dosing should be increased in increments of 5mg to allow for the use of 5mg tablets (e.g. a 50-54kg participant should receive 50mg). The recommended dose should be recorded in their medical records. It is recommended that oral prednisolone is taken in the morning.

### 7.3 Technique for intratympanic injection

**Pre-injection testing:** Immediately prior to the second and third intratympanic injections, a pure tone audiogram will be performed and analysed by the treating clinician.

---

**Stopping the intervention early:** If full recovery has been achieved, based on the pre-injection pure tone audiogram (return to within 10 dBHL of the unaffected ear at 0.5, 1.0, 2.0, 4.0kHz (if contralateral ear has no participant reported pre-existing loss)), the participant and clinician may jointly decide to omit further intratympanic injections. This will be recorded in the intervention Case Report Form (CRF) and the participant will continue within the trial.

**Preparing the medication:** Dexamethasone 3.3mg/ml or 3.8mg/ml should be administered depending on local availability and stored according to local policy. It is recommended that 1ml is drawn up in a 1ml syringe using a wide bore needle. A spinal needle (22-25 gauge) should then be attached to the syringe having removed the needle's central trochar. A slight bend at the hilt of the needle facilitates visualisation along the ear canal under a microscope.

**Positioning the participant for injection:** The procedure should be performed using a microscope or endoscope to visualise the tympanic membrane. The participant should lie recumbent on an examination table at an angle of <20 degrees, with the head turned slightly away from the side to be treated.

**Topical anaesthesia of the eardrum:** Any locally adopted method of local anaesthesia can be used, either in cream (most commonly EMLA (lidocaine 2.5% and prilocaine 2.5%)) or liquid form (most commonly co-phenylcaine spray (5% lidocaine + 0.5% phenylephrine) or xylocaine spray (10% lidocaine)). Local anaesthesia is not needed where there is a perforation of the eardrum.

- EMLA cream - The plunger is removed from a 2ml syringe to allow it to be filled with EMLA cream. The plunger is replaced and a blunt needle bent part way down the shaft to allow better visualisation during the application of EMLA cream to the eardrum under an outpatient microscope. It is important that the cream is in contact with the eardrum avoiding air gaps or bubbles. The anaesthetic can take 30 minutes to be effective.
- Co-phenylcaine or xylocaine spray – 4-6 sprays are administered directly into the ear canal with the study participant's head turned away to allow the liquid to remain in contact with the eardrum. The anaesthetic may take up to 10 minutes to be effective.

**Intratympanic injection:** Any local anaesthetic is removed using microsuction. Under visual guidance, the spinal needle should be passed through the tympanic membrane, ideally in the antero-superior quadrant in order to avoid the round window and ossicular chain. Dexamethasone is slowly injected, looking for the fluid level as it passes up the tympanic membrane. Once the middle ear is filled to the level of the needle, the needle can be withdrawn. Rapid filling of the middle ear should be avoided to reduce the risk of discomfort. The approximate volume of steroid injected into the middle ear should be recorded.

**Positioning the participant after injection:** Following the injection, the study participant should keep their head turned away from the injected ear and remain lying down in that position for 30 minutes to maximise uptake of steroid through the round window.

## 7.4 Technical training and competency for the intervention

Most clinicians will already practice intratympanic injection. However, some clinicians will not be familiar with the technique and all PIs and delegated staff performing intratympanic injection will be offered remote, or where necessary, face-to-face training.

---

Written material on the technique will be provided to sites. A video will also be available which will explain the participant positioning, setup and technical aspects of intratympanic injection. The training video will be available at: <https://entintegrate.co.uk/starfish>. Any clinician performing intratympanic injection within the trial will be required to review the training material.

Given that intratympanic injection is a simple procedure that is within the skill set of any ENT surgeon, only a self-assessment of competency and confirmation of training material review will be required. This will be recorded on a training log, which should be kept in the ISF and a copy forwarded to the STARFISH trial office. PIs will be responsible for approving trainee self-certification, and where ENT trainees have no or limited experience of the procedure, PI supervision is required.

## **7.5 Pregnancy**

Investigators should follow standard clinical practice by asking if a female of child bearing potential is, or could be pregnant, before prescribing oral steroid treatment. This will allow the investigator to tailor the pre-intervention counselling to the individual, in line with routine clinical practice. .

## **7.6 Drug interaction or contraindications**

### **7.6.1 Prohibited medications or treatments**

Any medication which is contraindicated in people taking oral steroid (Prednisolone) or intratympanic injection steroid (Dexamethasone) according to the British National Formulary will be prohibited.

### **7.6.2 Concomitant medications or treatments**

Oral and intratympanic steroid treatments have few drug interactions. In participants taking insulin or other medication for diabetes, additional care must be taken to regularly monitor blood glucose levels, and modify insulin dosing where indicated. Participants with diabetes will be provided with information on blood sugar control while on steroids or directed to their GP or diabetes specialist nurse.

## **7.7 Intervention modification or cessation**

As specified in section 7.3, complete resolution of hearing may allow intratympanic steroid treatment to be terminated after only one or two treatments. A rare complication of intratympanic injection is further hearing loss. Where this is observed on pure tone audiometry, no further treatments will be given. In the rare event that a study participant chooses to change treatment type or has a significant side effect from oral steroids and is advised to modify or stop the treatment by their treating clinician this will be recorded. On rare occasions, changes to the intervention schedule may be required based on participant request or adverse events. The allocated interventions may be discontinued if a participant requests to cease treatment or cross over to another arm. Adverse events such as allergic reaction, or a change in patient status, such as development of poor blood glucose control may alter the risk-benefit profile for that individual and the treating clinician should discuss this with the patient and alter the provided intervention, if required. Details of treatment

---

adherence, treatment modifications or treatment discontinuation at the Investigator's discretion should be documented in the source data.

Any modification of the interventions, or cross over to another trial arm will also be recorded on the CRFs.

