## **7.11 Adherence**

### **7.11.1 Adherence criteria**

A per protocol analysis will be performed for the primary outcome, and for the purposes of this, adherence to the oral steroid group will be defined as receiving prednisolone every day for 7 days, with treatment initiated within 4 weeks of symptom onset and not having the intratympanic treatment.

Adherence to intratympanic treatment group will be defined as receiving 3 intratympanic injections of dexamethasone (either 3.3 mg/ml or 3.8 mg/ml) spaced 7+/- 2 days apart, unless the course of injections was reduced to 1 or 2 injections on the basis of pure tone audiogram confirmed resolution of hearing loss or evidence of further sensorineural hearing loss, as well as not having received any oral steroid (prednisolone) with treatment initiated within 4 weeks of symptom onset. A reduction in course duration for intratympanic injection for any other reason will not be considered per protocol.

Adherence to the combined treatment group will require the criteria above to be met for both interventions. Additionally, if oral treatment is initiated within 4 weeks of symptom onset

---

then intratympanic treatment should be commenced up to four days preceding or following this.

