#### **Week 1 $\pm 2$ days after first injection**

The following should be performed in the intratympanic injection arm and combination treatment arm:

- Pure tone audiogram (0.5-8.0kHz range)
- 2nd intratympanic injection

NOTE: complete resolution of hearing may allow intratympanic steroid treatment to be terminated after only one treatment

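### A stop of injections required by section 7.7 for further hearing loss that is not shown to be sensorineural counts as non-adherent under section 7.11.1 (minor)

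*Protocol*

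**What the plan says.** Four places in the protocol bear on a shortened injection course.

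- **Section 7.7 (modification or cessation).** "A rare complication of intratympanic injection is further hearing loss. Where this is observed on pure tone audiometry, no further treatments will be given". The instruction is mandatory. It gives no type of loss, no size and no frequencies.
- **Section 7.11.1 (adherence criteria).** Fewer than three injections is still adherent if the course was cut "on the basis of pure tone audiogram confirmed resolution of hearing loss or evidence of further sensorineural hearing loss". Then: "A reduction in course duration for intratympanic injection for any other reason will not be considered per protocol". Oral adherence needs prednisolone on all 7 days, and the combined arm must satisfy both sets of criteria.
- **Section 7.3 (early-stopping paragraph).** This deals with full recovery only, as an option: "the participant and clinician may jointly decide to omit further intratympanic injections". Worsening is not mentioned.
- **Section 9 (visit notes at weeks 1 and 2).** These also mention recovery only. The week 1 note reads: "complete resolution of hearing may allow intratympanic steroid treatment to be terminated after only one treatment".

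Section 7.11.1 says the adherence definition serves the per-protocol analysis of the primary outcome. Section 14.2 makes that analysis secondary to intention-to-treat.

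**The concern.** Section 7.7 sets the stop and section 7.11.1 decides how that stop is classified, but they describe the trigger differently. The trigger in 7.7 is further hearing loss. The exemption in 7.11.1 is further sensorineural hearing loss, and its closing sentence leaves no room for anything else. Where the two descriptions part, a site that obeys 7.7 produces a protocol deviation under 7.11.1.

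The gap can occur in practice. The injection passes through the eardrum into the middle ear, and section 10.3 lists acute ear infection and persistent eardrum perforation among the adverse events to be reported. Either can worsen thresholds without being a further sensorineural loss.

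At stake is the make-up of the per-protocol set. Participants dropped by this route come only from the injection arms and are selected by a poor early audiogram, which is related to the outcome being compared.

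**Working it through.** The protocol states no figure for this, so the check is a comparison of passages, with two small calculations on scope.

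**1. Outcome by type of fall on the pre-injection audiogram**

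| Finding | Section 7.7 | Section 7.11.1 | Consistent? |
|---|---|---|---|
| Further sensorineural loss | Stop | Adherent (named exemption) | Yes |
| Conductive fall | Stop, read as written | Not per protocol | No |
| Mixed fall | Stop, read as written | Unclear; depends on whether a sensorineural part is accepted as evidence | Not settled |
| Fall not classified by type | Stop, read as written | Not per protocol unless treated as sensorineural | Not settled |

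The main case agrees. The mismatch is confined to the other three rows.

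**2. Can the combined-arm ambiguity arise?** It matters only if the audiogram before the second injection can fall inside the 7-day oral course.

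- Let s be the day of the first injection relative to the first oral day. Sections 7.11.1 and 9 allow s from −4 to +4.
- Let d be the days from the first to the second injection. Section 7.1 gives 7 ± 2, so d runs from 5 to 9.
- Oral day of that audiogram = 1 + s + d.
- Earliest: 1 − 4 + 5 = day 2. Latest: 1 + 4 + 9 = day 14.
- It falls within days 1 to 7 whenever s + d ≤ 6. At the nominal d = 7, that means the injection came at least one day before the oral course began.

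So the situation is possible. If the treatments to be withheld were read to include prednisolone, the participant would fail the 7-day oral criterion, which has no exception for a required stop.

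**3. Where the classification is used**

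- Primary analysis: intention-to-treat (section 14.2), so no effect.
- Per-protocol analysis of the primary outcome: affected in the intratympanic and combined arms.
- Internal pilot (section 8.1): green needs adherence of at least 90%, with 81 participants expected. Eight non-adherent gives 73/81 = 90.1%; nine gives 72/81 = 88.9%. Nine from all causes together would therefore move the pilot to amber. Section 8.1 does not say whether it uses the 7.11.1 definition, so this effect is conditional.

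**The case against.** The best reply is that 7.11.1 merely spells out what 7.7 abbreviates. In a trial of sensorineural loss, further loss is naturally sensorineural, and Table 5 lists complete sensorineural loss after injection as the expected serious event. Type of loss can usually be worked out: section 8.3.1 cites a procedure covering air and bone conduction, otoscopy is scheduled at both later injection visits, and section 9 defers testing when infection prevents it. This makes the affected group small. It does not close the gap, because 7.7 is unqualified and the last sentence of the exemption in 7.11.1 is absolute.

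On the combined arm, the opening of 7.7 uses the word treatments for injections a sentence or two earlier, so injections is the natural reading. That stands. What remains is that it is not stated.

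It is also fair that 7.7 lets a clinician modify or stop oral steroids for a significant side effect while 7.11.1 still asks for 7 days, so clinician-directed stops can leave the per-protocol set in any arm. Excluding incomplete courses is a legitimate choice. The point here is narrower: a stop on audiometry that the protocol itself orders, which only the injection arms have.

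Two stronger readings are tempting and are not supported:

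- **That 7.7 makes any measured worsening a stop, so that ordinary test-retest variation would halt many courses.** The sentence refers back to a rare complication, and section 7.3 has the treating clinician analyse the audiogram. Retest noise also says little about misclassification, since a shift accepted as further sensorineural loss would be adherent.
- **That 7.3 and the section 9 notes contradict 7.7.** They are silent on worsening. Section 7.7 refers to 7.3 and adds a rule to it. Silence can lead a site to overlook the rule, but it is not a conflict and does not itself create non-adherence.

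**Conclusion.** The point holds as a minor inconsistency between sections 7.7 and 7.11.1. A stop required by 7.7 can be classed as non-adherent when the fall is conductive, and the class is unsettled when it is mixed or not typed. The combined-arm wording adds a smaller ambiguity.

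Its size cannot be calculated from the documents, which give no rate of further loss and no split by type. That it is small rests on the protocol's own description of the complication as rare and on the existing exemption for sensorineural loss. A reader might infer bias in the main result. The documents do not support that: the primary analysis is by intention-to-treat, and the sample size does not depend on adherence. The exposure is limited to the per-protocol sensitivity analysis and, if it shares the definition, the pilot adherence rate.

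**What to change.** Reconcile the passages by wording:

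1. In section 7.11.1, replace the separate description of worsening with a reference to the stop in section 7.7, so that any stop the protocol requires is classified as adherent.
2. In section 7.7, state which treatments the stop covers in the combined arm. If the oral course is included, give the 7-day criterion in 7.11.1 the matching exception.
3. Add a cross-reference to 7.7 in the early-stopping paragraph of 7.3 and in the week 1 and week 2 notes of section 9.
4. In section 8.1, say whether pilot adherence uses the 7.11.1 definition.

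The type and amount of loss that should prompt a stop are for the trial team, and no view is taken here. The cost is a few sentences in an amendment. No new assessment is needed, because the audiogram before each later injection is already scheduled.

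The change makes the per-protocol set treat protocol-ordered stops in one way, and avoids removing injection-arm participants because of an early poor hearing result.
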